**Secondary outcomes**

**
*Hearing health outcomes*
**
Hearing handicap is measured by the Hearing Handicap Inventory Screening Questionnaire for Adults (HHIA). Participants’ self-reported hearing status is also collected to reflect subjective hearing impairment (HI). For the hearing aid use (HAU) group, the International Outcome Inventory for Hearing Aids (IOI-HA) will be used during the follow-up period to verify the treatment effects of HAU.Hearing-related health literacy is measured through a set of 9 questions developed by the research team based on the Knowledge, Attitude, and Practice theory. The 9-item assessment evaluates the respondents’ understanding (eg, information on hearing health, preventive measures, and awareness of available hearing health care), attitudes (eg, beliefs and attitudes toward hearing health care, willingness to prioritize and engage in hearing health activities), and behaviors (eg, regular hearing check-ups, protection from loud noises, the use of hearing aids if needed) related to hearing health [44]. The content and validity of the 9-item questionnaire were evaluated by 5 experts in hearing and health education.Communication ability is measured in the follow-up survey using the 10-item Self-Assessment of Communication (SAC), a self-report questionnaire designed to assess the impact of hearing loss and hearing intervention outcomes [45].
**
*Psychosocial and health-related outcomes*
**
Self-efficacy is assessed by the 10-item Chinese version of the General Self-Efficacy Scale (GSE). It has been identified as a good tool for measuring self-efficacy in community-dwelling adults [46].A sense of mastery is measured by the 7-item Chinese version Pearlin Mastery Scale (PMS). In addition to self-efficacy, mastery serves as another psychological resource that may help mitigate the impact of stressors on well-being. PMS has been regarded as a well-validated measure commonly used in studies to examine adults’ health and well-being outcomes [47].Psychological resilience in the HHE group is evaluated using the 2-item Connor-Davidson Resilience Scale (CD-RISC). The 2-item CD-RISC has demonstrated good validity and reliability in the elderly or Chinese general population [48].Quality of life includes both a subjective and an objective measure. Health-related quality of life is measured by standard tests such as the EQ-5D-5L, and subjective well-being is measured by the 5-item Chinese version of the Satisfaction with Life Scale (SWLS).

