**Methods:**

This study is a 3-arm, single-blinded, randomized controlled trial (RCT) with a follow-up at 24 months after the baseline study. A total of 435 participants aged 18 years and older with some degree of HI will be recruited and randomly assigned to 2 intervention groups and 1 control group. Free hearing-aid provision, as well as a hearing health education program that is combined with online and offline lessons, will be implemented in 2 intervention groups, respectively. The control group will not receive any intervention. The primary outcomes include social isolation and functioning in society. The secondary outcomes include social engagement, a sense of mastery, self-efficacy, psychological resilience, chronic diseases, life satisfaction, hearing health literacy, and hearing care usage.

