**Exclusion criteria**
Profound, complete, or total hearing loss or deafness: pure tone audiometry (PTA) at 4 frequencies for better ear of >90 dB HL, who are suggested to face challenges in effectively participating in the intervention setting [33].Significant ongoing ear-related diseases, medical contraindications to the use of hearing aids, or permanent conductive HI.Recent use of hearing aids or other listening devices: to assess the net effect of hearing interventions, participants should not be receiving any treatment for the HI already.Previous dementia diagnosis and self-reported mental health problems: self-reported diagnoses of dementia or memory-related diseases, and those who required a proxy to provide informed consent and answer questions due to cognitive problems or other mental health issues are excluded.Unwillingness to wear hearing aids regularly.Visual impairment: participants who are unable to see well enough (even with correction) to read a brochure or watch an online video are excluded.Unable or unwilling to provide written informed consent.

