Allocation										✓	✓		✓																			
Interventions																																
Hearing aids provision										✓											✓						✓					
Hearing health education											✓						✓							✓						✓		
Assessments																																
Sociodemographics										✓	✓		✓														✓			✓		✓
Hearing outcomes																																
Pure-tone audiometry										✓	✓		✓																			
HHIA^d^ score										✓	✓		✓														✓			✓		✓
Self-reported hearing										✓	✓		✓														✓			✓		✓
IOI-HA^e^ score																											✓					
Hearing-related health literary										✓	✓		✓														✓			✓		✓
Communication ability											✓		✓														✓			✓		✓
SWB^f^ (primary outcome)																																
LSNS-6^g^ score										✓	✓		✓		✓												✓			✓		✓
WHODAS 2.0^h^ score										✓	✓		✓		✓												✓			✓		✓
ISE^i^ score										✓	✓		✓		✓												✓			✓		✓
SEAQ^j^ score										✓	✓		✓		✓												✓			✓		✓
Secondary outcomes																																
GSE^k^ score										✓	✓		✓														✓			✓		✓
PMS^l^ score										✓	✓		✓														✓			✓		✓
CD-RISC^m^ score										✓	✓		✓														✓			✓		✓
EQ-5D-5L score										✓	✓		✓														✓			✓		✓
SWLS^n^ score										✓	✓		✓														✓			✓		✓
Covariates										✓	✓		✓														✓			✓		✓
Lifestyle behaviors										✓	✓		✓														✓			✓		✓
Chronic diseases										✓	✓		✓														✓			✓		✓

^a^T: hearing aid intervention group.

^b^T: hearing health education intervention group.

^c^C: control group.

^d^HHIA: Hearing Handicap Inventory Screening Questionnaire for Adults.

^e^IOI-HA: International Outcome Inventory for Hearing Aids.

^f^SWB: social well-being.

^g^LSNS-6: Lubben Social Network Scale.

^h^WHODAS 2.0: World Health Organization Disability Assessment Schedule 2.0.

^i^ISE: Index of Social Engagement.

^j^SEAQ: Social Engagement and Activities Questionnaire.

^k^GSE: General Self-Efficacy Scale.

^l^PMS: Pearlin Mastery Scale.

^m^CD-RISC: Connor-Davidson Resilience Scale.

^n^SWLS: Satisfaction with Life Scale.

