### Control Group

No interventions are provided for the control group considering the current situation of the HI rehabilitation:

Firstly, the prevalence of hearing aid usage in China is notably low, and there is a lack of health care awareness among rural older adults experiencing HI. A population-based survey carried out between 2014 and 2015 across 4 provinces in China, including Guangdong, revealed that the estimated prevalence of hearing aid acquisition among rural older adults with hearing loss is 4.2%. The reasons for not having a hearing aid within this group included “not understanding its function,” “not being able to afford it,” and “not needing it” [39]. According to the China Health and Retirement Longitudinal Study 2018 data, only 3% of older adults in rural areas with subjective hearing loss self-reported experience of using hearing aids [40]. Both sets of data indicate that they resonate with the natural setting for the control group.

Secondly, the policy context in Guangdong Province requires the attainment of a disability status qualification before the application for government-subsidized hearing aids, potentially discouraging older adults with HI from initiating the application process. The government offers subsidized hearing aids at institutions specifically established to provide services related to assistive devices for individuals with hearing disabilities. However, it is essential for these individuals to actively secure an official assessment to obtain a disability certificate, which is a prerequisite for applying for subsidized hearing aids. The process of obtaining disability status may be associated with social stigma, which could inhibit individuals from applying despite the availability of government subsidies. Therefore, the number of disabled individuals seeking these hearing aids remains relatively low.

Considering these 2 points, we have opted not to intervene with the older adults in the control group. Participants who are eligible for the control group are required to engage in both the baseline and follow-up surveys.

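### The hearing health literacy measure lists hearing-aid use among its behaviours, so if its items are summed, HAU comparisons on literacy partly measure receipt of the intervention

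*Protocol article*

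**What the plan says.** Textbox 2 (Secondary outcomes, hearing health outcomes) states: "Hearing-related health literacy is measured through a set of 9 questions developed by the research team". The set rests on Knowledge, Attitude and Practice theory. Its third component is described as "behaviors (eg, regular hearing check-ups, protection from loud noises, the use of hearing aids if needed) related to hearing health". The words at issue are "the use of hearing aids if needed".

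Other parts of the article bear on this:

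- **Status.** The Abstract (Methods) ends its list of secondary outcomes with "life satisfaction, hearing health literacy, and hearing care usage". Literacy and hearing care usage are thus named as separate outcomes.
- **Timing.** The Table 1 row printed as "Hearing-related health literary" is ticked for all three arms at baseline and at 24 months.
- **Intervention.** Under Study Design and Setting, the HAU arm receives hearing aids with follow-up instruction.
- **Entry.** The exclusion criteria remove recent users of aids or other listening devices, on the ground that "participants should not be receiving any treatment for the HI already".
- **Need.** The inclusion criteria require audiometric loss in everyone and describe the eligible grades as those likely to benefit from amplification.
- **Analysis.** Statistical Analysis compares control and intervention groups on primary and secondary outcomes by ANOVA and linear mixed-effects models. It makes no exception for the aid-use content.

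**The concern.** One of the behaviours the outcome is said to capture is the thing that the HAU arm is given. Use is close to zero in every arm at baseline because of the exclusion, so adjusting for baseline or analysing change does not remove the overlap. The qualifier about need does not remove it either, since all eligible participants have a loss for which the article says aids are likely to help.

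What is at stake is how a positive HAU result on literacy would be read. Improving hearing health literacy is a stated objective of the hearing health education (HHE) arm. If the total includes aid use, supplying devices could appear to teach, or could appear to match education on education's own target, when only possession and use of a device have changed.

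**Working it through.** The article gives no figure for the literacy outcome, so there is nothing to reproduce. The calculation below shows how large the overlap could be if the items are summed.

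**Inputs from the article**

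- Arm sizes: HAU 121, control 156 (Sample Size Calculation and Recruitment).
- Followed up at 24 months: 397 of 435 (Trial Status). Applied equally to each arm, this gives 121 × 397/435 = 110.4 and 156 × 397/435 = 142.4. Equal retention is an assumption.
- Control use, lower value: the Control Group section reports that "the estimated prevalence of hearing aid acquisition among rural older adults with hearing loss is 4.2" per cent.
- Control use, upper value: 20%, the planning allowance for control participants who take up aids.

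**Assumptions not in the article**

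- One aid-use item, scored 0/1, within a summed 0–9 total.
- SD of the total 1.5 to 2.5, equal in both arms.
- HAU use at 24 months 50% to 100%. The same 20% allowance applied to discontinuation would suggest 80%, but the Limitations section says that adherence to prolonged aid use is notably low, so 50% is included.
- No true difference in knowledge, attitude or any other behaviour.

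**Formulas**

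- Built-in difference = HAU use − control use, in points.
- Standardised difference d = built-in difference / SD.
- Standard error of d = √(1/110.4 + 1/142.4) = 0.127.
- Chance of p<0.05, two-sided = Φ(d/0.127 − 1.96) + Φ(−d/0.127 − 1.96).

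**Results**

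| HAU use | Control use | SD | Difference (points) | d | Chance of p<0.05 |
|---|---|---|---|---|---|
| 50% | 20% | 2.5 | 0.30 | 0.12 | 16% |
| 50% | 4.2% | 2.0 | 0.46 | 0.23 | 44% |
| 80% | 20% | 2.5 | 0.60 | 0.24 | 47% |
| 80% | 4.2% | 2.0 | 0.76 | 0.38 | 85% |
| 80% | 4.2% | 1.5 | 0.76 | 0.51 | 98% |
| 100% | 4.2% | 1.5 | 0.96 | 0.64 | 99.9% |

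The lowest case works out as 0.12/0.127 = 0.95, so Φ(−1.01) + Φ(−2.91) ≈ 0.16. With the aid-use content removed, the built-in difference is 0 and the chance returns to 5%.

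**The case against.** The strongest objection is that the article does not show the scoring. The behaviours are given as examples, with no item wording or response format and no statement that the nine answers are added up. Scores by domain fit the text equally well. In that case knowledge and attitude would be untouched, and the effect of aid provision would sit visibly in the practice domain. This objection stands. A reader might infer that the score certainly contains such an item and that free aids must raise it, but the article does not support that. The point is therefore conditional on a summed total.

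A reader might also infer that any HAU gain in literacy would be false. The article does not support this either. Practice is a declared part of the instrument, so taking up an aid is a real change in that domain. HAU participants also receive usage instruction, self-management materials, support one month after fitting, a WeChat group with audiologists and reinstruction at 12 months, so some real learning is plausible. What remains is that a total including aid use cannot separate learning from having a device.

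Nor should 80% use be read as a floor. It borrows a planning allowance, and the article itself expects low long-term adherence, which is why the illustration goes down to 16%.

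Finally, Statistical Analysis speaks of control against intervention groups and specifies no HAU versus HHE contrast on literacy. That part of the concern applies only if such a comparison is made.

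**Conclusion.** The overlap between the outcome's stated content and the randomised treatment is in the text, and nothing in the article removes it. If the items are summed, HAU versus control on literacy partly measures receipt of the intervention and may reach significance without any change in knowledge or attitude. Under the stated assumptions the built-in difference is 0.30 to 0.96 points (0.12 to 0.64 SD), with a 16% to 99.9% chance of p<0.05 against a nominal 5%. The range is wide because the item wording, the number of aid-use items, the scoring and the SD are all unknown. It is an illustration, not an estimate of bias in this trial.

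The scope is one secondary outcome. The primary outcomes do not use this measure, and the cost-effectiveness analysis rests on EQ-5D-5L. For HHE versus control, aid uptake is a legitimate behavioural response to education, so the full score can be interpreted there. This is a worthwhile, low-cost improvement and not a threat to the trial's main conclusions.

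**What to change.** Before unblinded analysis, specify the following for all three arms alike:

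- Compare literacy on the score without the aid-use content, or as separate knowledge, attitude and practice sub-scores. If sub-scores are used, state that the practice score includes aid use.
- Report hearing-aid use on its own under the hearing care usage outcome named in the Abstract.
- Give the full nine-item score as supplementary, interpretable mainly for HHE versus control.

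Using the same score in every arm matters because the planned ANOVA and mixed models cover three arms. Different versions for different contrasts would not fit one model, and the estimates would not be comparable.

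The cost is a short scoring rule with no new data. The small downside is a slightly shorter score than the one whose content the five experts assessed. Trial Status says that intervention effects were still unknown at the current protocol version, so on the article's account the rule could still be set without sight of the results.

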### Study Design and Setting

A three-arm, single-blinded RCT with a 24-month follow-up period will be conducted. A total of 435 eligible participants were randomly assigned in a 1:1:1 ratio to a control group, a hearing aid use (HAU) group, or an HHE group. The HAU group will receive hearing aids and follow-up instructions. Due to budget constraints, the audiological rehabilitation intervention predominantly used hearing aids provided by the Audiology Department of the Guangdong Provincial Cultural Sports and Rehabilitation Assistive Devices Center for People with Disabilities (GPSRC), which is affiliated with the China Disabled Persons’ Federation (CDPF). Individuals diagnosed with disabling HI and classified as persons with hearing disability are eligible to apply for complimentary hearing aids and fitting services from the local CDPF departments. Since the number of adults with HI who were eligible for hearing-aid fitting was limited to one site at the time of the baseline survey and intervention, a total of 139 persons with disabled HI were randomly selected from 4 sites with similar socioeconomic and cultural conditions. The selection was based on the list provided by GPSRC, which maintains records of hearing-disabled persons in Guangdong Province. The HHE group will undergo both offline and online educational interventions, while no interventions are planned for the control group that is similar to a natural setting. A sample of 278 adults diagnosed with some degree of HI was randomly selected and assigned to the HHE group and control group from Hualong County in Guangzhou, Guangdong, based on its roster. For the HAU group, participants were prescribed hearing aids at baseline (T0) and received reinstruction on the use of hearing aids 12 months after T0. For the HHE group, participants were required to participate in an offline hearing education at T0, followed by an online educational intervention at 6 months after T0, and an offline information intervention at 12 months after T0. The primary outcomes are social isolation and functioning, assessed at baseline and 24 months.

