
### Covariates

Sociodemographic factors (age, sex, residency, marital status, education, income status, and employment), lifestyle behaviors (smoking and drinking), and health conditions (visual status, diagnosed with hypertension, diabetes, or any other cardiovascular diseases, and self-reported health) of the eligible participants are collected during the baseline survey.

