### Statistical Analysis

The intent-to-treat principle will be used during the impact analysis. The differences between the control and intervention groups in terms of primary and secondary outcomes will be evaluated through ANOVA and linear mixed-effects modeling. Multiple methods such as weighting, matching, and imputation will be used to handle the problem of missing data and sample attrition. In addition, a nonparametric bias-corrected case resampling bootstrap method, structural equation modeling, or interaction analysis will be used to further explore the buffering effect of psychosocial factors. Heterogeneity analysis will be applied to investigate whether the intervention effects are robust across subgroup samples, such as participants with different levels of objective hearing loss.

The cost-effectiveness analysis will be based on the costs of the HAU or HHE interventions and their effects on improving health-related quality of life, as measured by EQ-5D-5L. EQ-5D-5L is designed to measure the generic quality of life in terms of mobility, self-care, usual activities, pain or discomfort, and anxiety or depression [49]. Previous literature has used this multidimensional construct of quality of life to evaluate the effect of hearing interventions [50-53].

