Third, the provision of free hearing aids may raise concerns regarding the social approval effect. Previous research on hearing aid interventions has typically involved the distribution of free devices [51,58,59]. In instances where there is a financial burden associated with acquiring commercial hearing aids, selection bias may arise, as economically disadvantaged older individuals may find it more challenging to participate in such interventions. The Chinese government has established a range of welfare policies aimed at supporting individuals with disabilities and the elderly, which include not only rehabilitation services, but also living subsidies for disabled individuals, long-term care insurance, and older adult care subsidies. Within this welfare framework, hearing aids do not represent a unique benefit. Therefore, we contend that the social approval effect remains within a manageable scope and is unlikely to compromise the reliability and validity of the RCT. Future research could also compare the intervention effects of paid hearing aids with those of free hearing aids.

Fourth, the interventions are conducted at different sites, which may result in geographical and selection biases. Nevertheless, the comparable socioeconomic and cultural contexts of these sites are expected to alleviate such biases. There was no pilot study due to time and budget constraints; however, given that the social and demographic characteristics of the feasibility study site closely resemble those of the formal trial sites, we believe this limitation does not pose a significant threat to the research design.

Fifth, our reliance on self-reported measures of social isolation and functioning may introduce measurement bias, which we will address through the use of validated tools, cross-validation, and multisource evaluations.

Lastly, although the sample size was determined using standard calculation methods, it remains relatively small, which affects its representativeness and external validity. Randomization in a small sample may not completely eliminate the preexisting differences either. Therefore, we will further use matching techniques or other econometric methods during the statistical analyses.

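### The HAU arm has no scheduled baseline for communication ability (SAC), and Table 1 and Textbox 2 disagree on its timing, so HAU versus control on this scale needs a hearing-adjusted, exploratory 24-month comparison

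*Protocol article*

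**What the plan says.** Two places in the protocol article fix when communication ability is measured.

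- Textbox 2, secondary outcomes: "Communication ability is measured in the follow-up survey using the 10-item Self-Assessment of Communication (SAC". No baseline administration is stated for any arm.
- Table 1, row "Communication ability": ticks at Day 0 for HHE and control, a blank for HAU, and ticks for all three arms at 24 months.

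On analysis, the Statistical Analysis section says: "The differences between the control and intervention groups in terms of primary and secondary outcomes will be evaluated through ANOVA and linear mixed-effects modeling". SAC is listed among the secondary outcomes.

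On where the arms come from, Study Design and Setting says of HAU that "a total of 139 persons with disabled HI were randomly selected from 4 sites", using a provincial list of hearing-disabled persons. The HHE and control arms come from a single county roster of adults with some degree of hearing impairment.

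The Covariates section lists sociodemographic and lifestyle variables and "health conditions (visual status, diagnosed with hypertension, diabetes, or any other cardiovascular diseases, and self-reported health"; none is a hearing measure. Objective hearing loss enters the analysis section only as an example of a subgroup: "such as participants with different levels of objective hearing loss". The Limitations section adds that "we will further use matching techniques or other econometric methods during the statistical analyses", without naming variables.

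**The concern.** The two statements of the SAC schedule cannot both be right for HHE and control, and on either one HAU has no baseline.

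A missing baseline does little harm when arms are randomised from one pool: the 24-month means are still comparable, only less precisely. HAU versus control does not have that protection as the design is described, because the two arms were selected from different lists at different sites. For the other between-arm scales, the outcome's own Day 0 score can at least be used to correct a starting difference. For SAC in HAU it cannot. A plain 24-month ANOVA would then report the sum of the starting difference and the intervention effect.

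A mixed model does not rescue this. If it used Day 0 scores from HHE and control only, it would have to assume that HAU started at the same level, which the separate sampling gives no reason to believe.

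**Working it through.** **1. The schedules side by side**

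| Source and row | HAU Day 0 | HHE Day 0 | Control Day 0 | 24 months |
|---|---|---|---|---|
| Textbox 2, SAC | not stated | not stated | not stated | follow-up survey |
| Table 1, communication ability | blank | tick | tick | all three arms |
| Table 1, HHIA | tick | tick | tick | all three arms |
| Table 1, pure-tone audiometry | tick | tick | tick | none |

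The communication row has five ticks and the HHIA row six. The missing one falls in the column where the hearing-aid provision row has its Day 0 tick, which is the HAU column. Table 1 should not be trusted alone: its four social well-being rows also carry a 6-month tick for HAU only, while Study Design and Setting places the primary outcomes at baseline and 24 months. If Table 1 is set aside, Textbox 2 still gives no HAU baseline.

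**2. The plan's own figure**

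The plan gives no figure for SAC. Its one calculation, for WHODAS 2.0, reproduces: n = 2(1.960 + 1.036)²/0.404² = 110.02, rounded up to 111 per group. With 20% loss, 111/0.8 = 138.75, so 139 per arm, which matches the 139 selected for HAU and 278 = 2 × 139 for the other two arms.

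**3. Are HAU and control alike at baseline?**

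Standardised differences (HAU minus control) from Table 2:

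- Age: (67.02 − 74.82)/√[(9.29² + 11.75²)/2] = −7.80/10.59 = −0.74.
- Poor economic status, 96/120 against 39/154: (0.800 − 0.253)/√[(0.160 + 0.189)/2] = 1.31.
- Poor self-rated health, 23/121 against 15/156: (0.190 − 0.096)/√[(0.154 + 0.087)/2] = 0.27.

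Sex is not used, because the arm counts sum to 187 men and 247 women while the Total column shows the reverse. Chronic disease is not used, because only 110 of 156 controls have data. HAU is younger but poorer and in worse self-rated health, so the sign of any SAC gap cannot be inferred. These three variables correspond to listed covariates and can be adjusted for. They show only that the arms are not interchangeable.

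**4. Precision at 24 months**

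Retention is 397/435 = 0.913. Assuming it is even across arms, 121 × 0.913 ≈ 110 HAU and 156 × 0.913 ≈ 142 control. SE = √(1/110 + 1/142) = 0.127 SD; 95% half-width = 1.96 × 0.127 = 0.25 SD.

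**5. What a starting gap would do (illustration, all gaps assumed)**

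A gap of g SD that persists shifts the unadjusted difference by g. With no true effect, the chance of nominal significance is Φ(−1.96 − g/SE) + 1 − Φ(1.96 − g/SE):

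| g (SD) | 0 | 0.1 | 0.2 | 0.3 | 0.4 |
|---|---|---|---|---|---|
| Chance | 5% | 12% | 35% | 66% | 88% |

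If covariates removed half of the gap, the chance would fall from 35% to 12% at g = 0.2 and from 88% to 35% at g = 0.4. The article gives no correlation between SAC and hearing threshold or HHIA, so the share they would actually remove is unknown.

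**The case against.** The strongest reply has five parts.

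- **One blank cell.** Only Table 1 separates HAU from control, and that table has other oddities. On Textbox 2 alone, SAC is a follow-up-only scale in every arm, which is a legitimate choice. This stands, so the forms have to decide. It does not remove the problem, because HAU lacks a baseline on both readings.
- **A generic sentence.** The analysis sentence covers secondary outcomes as a class and cannot bind every scale; IOI-HA, for example, is collected in HAU only. ANOVA can also handle a 24-month-only outcome. Both points are fair. But SAC is ticked in all three arms at 24 months, so a HAU–control comparison is the natural reading, and an unadjusted ANOVA is the version that goes wrong.
- **Covariates belong in the analysis plan.** A reader might infer that hearing measures will be left out of the adjustment. The article does not say so: the Covariates section lists what is collected and is not described as a closed set. What can be said is that the article states ANOVA and mixed models without a remedy for an arm that has no outcome baseline.
- **Existing safeguards.** The article stratifies randomisation by severity and site, admits geographical and selection bias, and promises matching. Stratification cannot balance arms selected from different lists and sites, and matching on unnamed variables cannot use a SAC score that HAU does not have.
- **A trial-wide cause.** Separate sampling affects every HAU–control comparison, not just SAC. This stands. SAC differs only in that its own baseline is unavailable for correction.

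**Conclusion.** The schedule conflict is certain. That HAU has no scheduled SAC baseline follows from both sources, subject to the stored forms. Given the separate sampling, an unadjusted 24-month HAU–control comparison of SAC cannot be read as an intervention effect.

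Severity is low. One secondary scale is affected, it is absent from the abstract's outcome list, and the primary outcomes have Day 0 scores in all arms.

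A reader might go further and infer that the SAC result will be biased by a known amount or in a known direction. The documents do not support that: they contain no SAC data, the Table 2 imbalances point both ways, and the percentages above rest on assumed gaps and even retention.

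A reader might also infer that resilience (CD-RISC) is missing outside HHE, because Textbox 2 ties it to that group. Table 1 ticks it in all arms and the abstract lists resilience without restriction, so this is probably a wording slip that needs only a text correction.

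**What to change.** 1. Check the stored baseline forms to see which arms have SAC, and correct Table 1 or Textbox 2 so that they agree.
2. If HAU has no baseline SAC, define HAU versus control as a 24-month comparison adjusted for Day 0 better-ear pure-tone threshold and HHIA, both scheduled in all arms, plus the listed covariates.
3. Check that HAU and control overlap on hearing threshold. HAU came from a disabling-impairment list and control from people with some degree of impairment, so overlap may be limited. If it is, restrict the comparison to the overlapping range.
4. Report the result as exploratory. Site largely coincides with arm, and covariates cannot remove site or residual confounding.
5. Use a change or baseline-adjusted SAC model only for HHE versus control, and only if their Day 0 scores exist.

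The cost is a check of the forms, a text correction, two added covariates and one overlap check. Any restriction to the overlapping range would lose some participants and precision. No new data are needed, and a missing baseline can no longer be collected, since follow-up took place in September 2024. Trial Status says intervention effects were still unknown at this protocol version, so on that statement the change can be fixed before results are seen.
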